### Study participants

We aim to recruit 3000 participants from primary care networks in NE England

### Inclusion criteria

Individuals aged 18–80 years attending for an ‘annual review of care’, ‘chronic disease review’ or ‘health check’ with one or more of the following risk factors:

Obesity (BMI>30 kg/m^2^).T2DM.Potentially hazardous/harmful alcohol consumption (AUDIT score>8).^33^

### Exclusion criteria

Life limiting disease on high risk or palliative care register.Known liver disease under secondary care follow-up.Lack of capacity to provide informed consentPatient unable to understand or speak English.

### Study outcomes

#### Primary outcome

The primary outcome of SOLID is to assess the number of patients identified with advanced liver fibrosis/cirrhosis using each of the pathways based on an overall clinical evaluation by a panel of hepatologists.

The presence of advanced fibrosis will be determined by an overall clinical assessment after secondary care review and will include all investigations undertaken in primary and secondary care. Where there is uncertainty about the stage of liver fibrosis, a liver biopsy will be offered as per usual clinical care. The overall clinical assessment for advanced fibrosis will be undertaken by three hepatologists. Where cases are equivocal, all the clinical data for these patients will be reviewed independently by each of the hepatologists to determine the presence of advanced fibrosis. An agreement analysis will be conducted to determine the concordance between hepatologists. Discrepancies will be resolved by consensus.

#### Secondary outcomes

Assess the utility of non-invasive testing/triage strategies to identify patients who have liver-related events (death, hepatic decompensation and transplantation) during longitudinal follow-up at 2, 5 and 10 years via electronic care records/NHS Digital.Compare the number of new cases of advanced fibrosis/cirrhosis identified with previous years in participating practices and control practices historically and over the study period.Assess the performance of FIB-4, ELF, PRO-C3 and other novel blood-based biomarkers alone or in combination to identify advanced fibrosis/cirrhosis as defined by overall clinical assessment or LSM.Assess the performance of the biomarkers to correctly exclude advanced fibrosis/cirrhosis.Assess the uptake of the liver assessment, attendance rates for VCTE and liver clinic appointments with both pathways.Conduct a subsequent cost effectiveness analysis of established and novel pathways.Assess barriers and facilitators to incorporating the pathway into routine primary care practice.Development of the optimum pathway (clinically and cost-effective and implementable) for further evaluation.

### Recruitment and consent

Potential participants will be identified prior to their review appointment. An invitation to the study and Participant Information Sheet (PIS) will be sent via post, email or text prior to their appointment as per the practice’s usual procedure.

The study will use electronic remote consent. Within their invitation letter, patients will be given log in details for the study consent portal where they can give consent and then input some clinical details to assess their eligibility for the study (current weight and height to determine BMI, known history of T2DM and AUDIT score^33^). A member of the research team will support individuals to complete the consent process. Patients who meet the eligibility criteria and give consent will then be asked to complete some data collection fields (eg, ethnicity, alcohol consumption, smoking history, EQ-5D-L^34^). When patients attend for their review appointment, study staff will confirm consent (verbally and document in the electronic patient record). Study procedures (table 1) will then be performed at the annual review.

**Table 1 T1:** Study procedures

Clinical data collected	Blood samples
Date of birth	FBC
Age at time of assessment	Liver enzymes (albumin, bilirubin, ALT, ALP)
Sex at birth	AST
Ethnicity	GGT
Weight	HbA1c
Height	FIB-4 score
BMI	Lipids
Waist and Hip circumference	ELF
Blood pressure	PRO-C3
AUDIT score^33^	Blood for storage to assess future novel biomarkers of liver disease
Current alcohol consumption (average units/week over last year)	
History of previous heavy alcohol consumption (>35 U/week for females or >50 U/week for males) for >1 year	
Smoking history	
Relevant medical history including: hypertension, T2DM, dyslipidaemia, obstructive sleep apnoea	
Current medications	
EQ-5D-L questionnaire^34^	

ALP, alkaline phosphatase; ALT, alanine aminotransferase; AST, aspartate aminotransferase; AUDIT, Alcohol Use Disorders Identification Tool; ELF, enhanced liver fibrosis test; EQ-5D-L, EuroQol-5 Dimensions-Level; FBC, full blood count; GGT, gamma glutamyl transferase; T2DM, type 2 diabetes.

For individuals who would like to take part but do not want to use remote electronic consent, informed consent discussions will be undertaken by trained staff in accordance with good clinical practice (GCP) and study procedures performed at the annual review.

A screening log will be kept to document details of subjects invited to participate in the study. This will be to CONSORT (CONsolidated Standards Of Reporting Trials) recommendations to ensure data available within the observational cohort are not influenced by unexpected bias in those declining participation. The log will also ensure that potential participants are only approached once.

### Study procedures

All participants will have a liver fibrosis assessment using established biomarkers (VCTE and/or FIB-4 and ELF), blood tests and relevant clinical and demographic data collected at the time of assessment, as shown in table 1.

The optimum clinical pathway for the evaluation of liver fibrosis is not known so we plan to evaluate two pathways (figure 1) to determine which is most clinically and cost-effective. In pathway one, all patients will be offered VCTE and have blood tests for liver fibrosis biomarkers. In pathway two, patients with FIB-4>1.3 and/or ELF>9.8 indicating possible advanced fibrosis/cirrhosis will have VCTE to stage fibrosis.

VCTE will be conducted by trained operators at Newcastle Hospitals or in the primary care centre depending on the proximity of primary care sites to the hospital (sites close to the hospital will have VCTE performed at the hospital and those further away will have it performed at the practice). LSMs and controlled attenuation parameter readings will be obtained using a Fibroscan 430 mini+machine with M or XL probe as per the manufacturer’s recommendations. VCTE reading will be considered ‘reliable’ if they meet the accepted quality criteria of at least 10 readings from the same location with a single probe and the IQR/median ratio is less than 30% when the LSM exceeds 7.1 kPa.^35^

Individuals will be given a report of their liver assessment (LSM or FIB-4/ELF) to indicate their stage of liver fibrosis. All participants will be given relevant lifestyle advice and an information booklet entitled ‘Looking after your Liver’ (online supplemental file 1).

10.1136/bmjgast-2022-001092.supp1Supplementary data

Individuals with an LSM<8 kPa or who have low FIB-4/ELF (pathway 2), which excludes advanced fibrosis, will remain in primary care with further monitoring as per their usual care. Individuals with an LSM>8 kPa, indicating possible moderate to advanced liver fibrosis, will be referred to secondary care for further assessment and treatment. VCTE has a failure rate of approximately 5%. For individuals where it is not possible to obtain a reliable LSM, the ELF test and FIB-4 will be used as an alternative test to assess fibrosis. Both the FIB-4 and ELF tests can reliably exclude advanced fibrosis in patients with fatty liver disease.^13 14^ Individuals with a low ELF (<9.8) and FIB-4 score (<1.3) will be managed in primary care, while those with an ELF>9.8 and/or FIB-4 score>1.3 will be referred to secondary care for further assessment.

Individuals with raised liver blood tests will have investigations as per standard care following the Northeast and North Cumbria Abnormal Liver Blood Test Guidelines.^36^

### Secondary care assessment for individuals with suspected moderate/advanced liver fibrosis

Investigations and management in secondary care will be conducted as per usual clinical practice (including clinical history and examination, blood liver aetiology screen, liver ultrasound and liver biopsy or other imaging, where appropriate).^30 31^ Management will depend on the underlying diagnosis and stage of liver fibrosis. Relevant clinical data will be collected from the patients’ clinical encounters in secondary care including:

Final stage of liver fibrosis determined by overall clinical assessment using all available results (primary endpoint).Secondary care diagnosis of cause of liver disease.Details of further investigations carried out as per usual clinical care (blood tests, imaging, liver biopsy).Relevant medical history and medications.Health-related quality of life questionnaire (CLDQ, Chronic Liver Disease Questionnaire).^37^

### Proposed analyses in the study

#### Description of the cohort

The baseline characteristics of the cohort and primary and secondary outcomes will be described using descriptive statistics.

#### Assessment of the performance of the biomarkers

Diagnostic accuracy of the biomarkers will be assessed using the primary and secondary endpoint reference standards. The performance of the non-invasive tests to identify advanced fibrosis will be assessed by receiver operating characteristic curve analysis. The sensitivity, specificity, positive predictive values, negative predictive values, positive likelihood ratios (LR+ve) and negative likelihood ratios (LR−ve) will be calculated for each test or combination of tests using established cut-offs. A number of post hoc analyses will be conducted including the assessment of the performance of age specific cut-offs for the FIB-4 score to diagnose/exclude advanced fibrosis^22^ and a review of the performance of the biomarkers in subsets of patients with suspected NAFLD, ARLD and metabolic dysfunction associated fatty liver disease.^38^ Moreover, we will assess the impact of combinations of liver disease risk factors and other metabolic risks (eg, pre-diabetes, hypertension and dyslipidaemia) in identifying advanced liver disease. The clinical efficacy of pathways to detect advanced fibrosis using the biomarkers alone or in combination will be modelled using the data obtained from the study to develop optimal pathways.

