#### Sample size calculation and power estimates

This study will recruit 3000 participants from Primary Care Networks in Northeast England. Searches in two practices indicate that at least 2600 of 20 000 patients meet the eligibility criteria and attend annual year of care reviews. In addition, approximately 200 patients attend 5-yearly health reviews. Approximately 1500 patients will be recruited into each pathway. We estimate that the prevalence of moderate/advanced fibrosis in the recruited population will be 5%–7.5%.^9 39 40^

With a prevalence of advanced fibrosis of 5%–7.5%, this will give us 150–225 true positives and 2775–2850 true negatives. The large sample of true negatives will result in higher precision to estimate specificity than sensitivity. The total sample size of 3000 will provide a precise estimate of the true prevalence for this population. If the true prevalence is 5%–7.5%, the expected width of the 95% CI for the population prevalence is 0.06–0.019.

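### In pathway 2 the FIB-4/ELF result decides who can receive a reference diagnosis, so accuracy pooled over all 3000 participants carries partial verification bias

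*Protocol article*

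**What the plan says.** The section on biomarker performance states: "Diagnostic accuracy of the biomarkers will be assessed using the primary and secondary endpoint reference standards". It plans ROC analysis, sensitivity, specificity, predictive values and likelihood ratios for each test or combination, and does not restrict them by pathway.

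There are two reference standards. Under Primary outcome, the panel's overall clinical assessment is made after secondary care review. Under Secondary outcomes, LSM is the alternative, and LSM requires VCTE.

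Study procedures offers VCTE to everyone in pathway 1. For the other pathway it says: "In pathway two, patients with FIB-4>1.3 and/or ELF>9.8 indicating possible advanced fibrosis/cirrhosis will have VCTE to stage fibrosis". On those below both cut-offs it says: "Individuals with an LSM<8 kPa or who have low FIB-4/ELF (pathway 2), which excludes advanced fibrosis, will remain in primary care".

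The sample size section says "Approximately 1500 patients will be recruited into each pathway" and "With a prevalence of advanced fibrosis of 5%–7.5%, this will give us 150–225 true positives and 2775–2850 true negatives". The next sentence there links these counts to the precision of specificity and sensitivity.

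**The concern.** In pathway 2 the tests under evaluation control access to both reference standards. A person with advanced fibrosis but low FIB-4 and low ELF is a false negative of the triage rule. That person has no LSM and no secondary care review, and so cannot ordinarily be counted as one. The Introduction itself says that these tests have not been systematically evaluated in unselected primary care, so their ability to exclude disease there is a question for the study and cannot be assumed when disease status is assigned.

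The estimates at risk are those that bear on rule-out. Correct exclusion of advanced fibrosis is a listed secondary outcome. The Strengths section says the design should show whether VCTE can be targeted more narrowly, and study results are to feed pathway and cost-effectiveness models. An inflated sensitivity for FIB-4/ELF would favour omitting VCTE. The Limitations section discusses the lack of biopsy, but not that verification depends on the index tests.

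**Working it through.** **The plan's own counts.** 3000 × 5% = 150 and 3000 × 7.5% = 225 with disease; 2850 and 2775 without. Both reproduce, and only with 3000 as the denominator. What the article calls true positives and true negatives are therefore people with and without disease among all participants. The design cannot verify that many.

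**Inputs.** About 1500 per pathway and prevalence 5–7.5% (sample size section). The sensitivity s and specificity of the triage rule in this population are not given. Assumed here: s from 0.70 to 0.90, specificity 0.60, equal prevalence in both pathways, complete attendance, and VCTE plus panel taken as truth.

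**Sensitivity of the combined rule.** Let each pathway contain N true cases.
- Pathway 1: N cases verified, sN of them triage-positive.
- Pathway 2: sN cases verified, all triage-positive; (1−s)N unseen. Apparent sensitivity is sN/sN = 100%, whatever s is.
- Pooled: (sN + sN)/(N + sN) = 2s/(1+s).

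| Assumed s | Pooled 2s/(1+s) | Unseen cases in pathway 2, prevalence 5% | Unseen cases, prevalence 7.5% |
|---|---|---|---|
| 0.70 | 1.4/1.7 = 0.82 | 75 × 0.30 = 22.5 | 112.5 × 0.30 = 33.8 |
| 0.80 | 1.6/1.8 = 0.89 | 15.0 | 22.5 |
| 0.90 | 1.8/1.9 = 0.95 | 7.5 | 11.2 |

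**Effect of the raised-liver-test route.** Suppose it finds a fraction r of the unseen cases. The pooled figure becomes 2s/[1 + s + r(1−s)]. With r = 0.5 (an assumption) this is 1.4/1.85 = 0.76, 1.6/1.9 = 0.84 and 1.8/1.95 = 0.92. The bias shrinks but remains.

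**The other measures depend on how unverified people are handled.** Take s = 0.80, specificity 0.60, prevalence 7.5%. Each pathway then has 90 triage-positive cases, 22.5 triage-negative cases, 832.5 triage-negative non-cases and 555 triage-positive non-cases.
- Labelled non-cases: NPV rises from 832.5/855 = 97.4% to (2 × 832.5 + 22.5)/(2 × 855) = 98.7%. Specificity hardly moves.
- Dropped: the remaining triage-negatives all come from pathway 1, so NPV stays at 97.4%. Specificity falls from 60% to 832.5/(832.5 + 2 × 555) = 43%.
- Sensitivity is 0.89 in both cases.

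**Single markers.** A simulation assumed sensitivity/specificity of 70/70% for FIB-4, 65/85% for ELF and 65/80% for PRO-C3. The markers were either conditionally independent or correlated at 0.3–0.5. Pooled sensitivity was 74–76% for FIB-4, 69–70% for ELF and 65–67% for PRO-C3. The rise is smaller for FIB-4 or ELF alone because the other test can still lead to VCTE.

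**Cases available in pathway 1.** 1500 × 5% = 75 and 1500 × 7.5% = 112.5. Removing the roughly 5% VCTE failures: 75 × 0.95 = 71 and 112.5 × 0.95 = 107.

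**Precision.** Wilson 95% half-widths at 80% sensitivity are about 9 points with 75 cases and 7 with 112, against about 6 with 150 and 5 with 225. With 71 and 107 cases they are about 9 and 7.5.

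**The case against.** The strongest reply is that the performance section names no denominator, and that an analysis plan not shown here may restrict the analysis set or handle missing reference results. It is correct that pooling is inferred and not declared. Likewise, the remark that low FIB-4/ELF excludes advanced fibrosis explains why people stay in primary care; it is not an explicit rule for labelling them non-cases. But the sample size section rests the precision of sensitivity and specificity on "this will give us 150–225 true positives and 2775–2850 true negatives", and those counts need a known status for all 3000. That is a statement in this document that the design cannot deliver.

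A reader might also infer more than the documents support:
- *Every marker is inflated by 2s/(1+s).* The formula applies only to the combined FIB-4/ELF rule. PRO-C3 does not decide who has VCTE.
- *NPV and ROC area must be inflated.* This depends on how unverified people are handled, which the article does not state. If they are dropped, NPV of the combined rule is not inflated, specificity falls, and the direction for ROC area is not established.
- *No weighting could repair it.* That holds within pathway 2. In the pooled data, triage-negatives in pathway 1 are offered VCTE, so a correction can borrow from them if the pathways are comparable.
- *Pathway 1 is free of the problem.* It is not for the panel standard: an LSM below 8 kPa keeps people out of secondary care review there too, and the panel sees all results, FIB-4 and ELF included.

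Two mitigations are real but partial. Raised liver tests lead to standard investigation, though the Introduction says up to half of patients with advanced disease have normal enzymes. Record follow-up at 2, 5 and 10 years is intended to address missed disease, but through liver-related events and mortality, not through the baseline reference standard.

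**Conclusion.** The concern holds in this form. With accuracy unrestricted by pathway and the counts set over 3000, the plan leads to a pooled sensitivity for the combined FIB-4/ELF rule that is too high under either handling of unverified participants: by about 12, 9 and 5 points at assumed true values of 0.70, 0.80 and 0.90, less if raised liver tests bring some missed cases to light. In pathway 2 alone it is about 100%, with the same exception. The direction for sensitivity follows from the design; the size rests on the assumed s, equal pathways and full attendance. The effect is smaller for FIB-4 or ELF alone, and for PRO-C3 sensitivity it depends on correlation with them. The primary outcome, the number identified by each pathway, is not affected.

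**What to change.** - Base the main estimates of sensitivity, specificity, PPV, NPV, likelihood ratios and ROC on pathway 1, where VCTE is offered whatever the blood results, with LSM as the cleaner reference for the blood markers. Treat VCTE failures as unverified, since FIB-4 and ELF decide their referral.
- In pathway 2, report yield and the PPV among triage-positives.
- Add a pooled analysis only as a sensitivity analysis, with a verification-bias correction (for example Begg-Greenes) that borrows the pathway 1 triage-negatives and states the assumption that the pathways are comparable.
- Restate the cases available for accuracy as about 75–112, or about 71–107 after VCTE failures, instead of 150–225.
- State that panel-based accuracy remains limited even in pathway 1, for the reasons given above.

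The cost is analysis wording, one restated count and a wider interval: at 80% sensitivity, about ±7–9 points instead of about ±5–6. No further participants or procedures are needed.

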#### Sample size calculation and power estimates

This study will recruit 3000 participants from Primary Care Networks in Northeast England. Searches in two practices indicate that at least 2600 of 20 000 patients meet the eligibility criteria and attend annual year of care reviews. In addition, approximately 200 patients attend 5-yearly health reviews. Approximately 1500 patients will be recruited into each pathway. We estimate that the prevalence of moderate/advanced fibrosis in the recruited population will be 5%–7.5%.^9 39 40^

With a prevalence of advanced fibrosis of 5%–7.5%, this will give us 150–225 true positives and 2775–2850 true negatives. The large sample of true negatives will result in higher precision to estimate specificity than sensitivity. The total sample size of 3000 will provide a precise estimate of the true prevalence for this population. If the true prevalence is 5%–7.5%, the expected width of the 95% CI for the population prevalence is 0.06–0.019.

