### Strengths

This is one of the first studies to systematically assess the performance of multiple liver fibrosis biomarkers in a large cohort of well-phenotyped participants from primary care. We are recruiting from a variety of primary care settings, including the inner city and rural areas to make the findings widely applicable. Crucially, in addition to assessing biomarker performance to detect advanced fibrosis at baseline, we are collecting data on long-term outcomes for up to 10 years to assess the prognostic ability of biomarkers for liver-related outcomes, which has never been assessed in this setting.

A major strength of this study is that we are running the study close to ‘real life’ to facilitate recruitment and enable widespread implementation after the study. The liver health checks are being conducted during established primary care chronic disease reviews and health checks, which is an efficient use of resources since much of the information required is already collected. Remote electronic consent will enable many of the research elements of the study (eg, questionnaires) to be conducted electronically prior to the annual review appointment, meaning healthcare assistants can focus on conducting the key clinical aspects like obtaining blood tests and taking anthropometric measurements. Many of the participants will require an additional appointment for VCTE to stage liver fibrosis as this is a key fibrosis endpoint for the study. The design of our study will allow us to determine whether VCTE can be used in a more targeted manner.

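### The expected confidence-interval width for prevalence treats participants recruited through general practices as a simple random sample, and its lower figure does not reproduce

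*Protocol article*

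**What the plan says.** The protocol article, under Sample size calculation and power estimates, states that "This study will recruit 3000 participants from Primary Care Networks in Northeast England" and that "Approximately 1500 patients will be recruited into each pathway". It takes a prevalence of 5% to 7.5%, from which "this will give us 150–225 true positives and 2775–2850 true negatives", and concludes that 3000 people will estimate the population prevalence precisely: "the expected width of the 95% CI for the population prevalence is 0.06–0.019". This is the only precision figure in the document. No number of practices, ICC or design effect appears.

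The same section gives an idea of practice size: "Searches in two practices indicate that at least 2600 of 20 000 patients meet the eligibility criteria and attend annual year of care reviews".

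Under Strengths the article says: "We are recruiting from a variety of primary care settings, including the inner city and rural areas to make the findings widely applicable". Under Study procedures, the place of elastography is settled site by site: "sites close to the hospital will have VCTE performed at the hospital and those further away will have it performed at the practice".

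**The concern.** Participants enter through their practice's annual review, so they arrive in groups. If practices differ in the prevalence of advanced fibrosis among those recruited, two people from the same practice are more alike than two people from different practices, and 3000 participants carry less information than 3000 independent ones. The Strengths section says that settings are varied so that findings apply widely. An interval meant to support inference beyond the recruited practices has to include the variation between them.

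At stake is the claim that the sample gives a precise prevalence estimate. Precision is already lower for each pathway, which has about half the sample, and the primary outcome is the number identified by each pathway. Site-level arrangements for elastography could also make attendance, a secondary outcome, vary by practice.

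**Working it through.** **Inputs from the protocol article:** n = 3000 in total and about 1500 per pathway; prevalence p = 5% to 7.5%; 95% confidence (z = 1.96); printed width 0.06–0.019; at least 2600 eligible patients in two practices, about 1300 each.

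**Inputs assumed, because the document gives none:** recruits per practice m, and ICC.

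**Step 1. Reproduce the printed width.** Full width under independence = 2 × 1.96 × √(p(1−p)/n).

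- p = 7.5%: 3.92 × √(0.075 × 0.925/3000) = 0.0189. This matches the printed 0.019, with a design effect of 1.
- p = 5%: 3.92 × √(0.05 × 0.95/3000) = 0.0156. This does not match the printed 0.06.

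Other readings do not rescue 0.06. At 5%, the half-width is 0.0078, the Wilson width 0.0156, the Clopper-Pearson width 0.0159, and the width for n = 1500 is 0.0221. Clustering does not explain it either: 0.06 would need a design effect of (0.06/0.0156)² ≈ 14.8 at the 5% end, while 0.019 needs about 1.02 at the 7.5% end. A misprint of 0.016 is the most plausible explanation.

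**Step 2. Allow for practice.** Design effect = 1 + (m − 1) × ICC; clustered width = independent width × √(design effect); effective n = 3000/(design effect).

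| Practices | m | ICC | Design effect | Width at 5% | Width at 7.5% | Effective n |
|---|---|---|---|---|---|---|
| any | any | 0 | 1.00 | 0.0156 | 0.0189 | 3000 |
| 30 | 100 | 0.001 | 1.10 | 0.0164 | 0.0198 | 2730 |
| 20 | 150 | 0.01 | 2.49 | 0.0246 | 0.0297 | 1205 |
| 10 | 300 | 0.02 | 6.98 | 0.0412 | 0.0498 | 430 |

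With about 1300 eligible per practice, 100 to 300 recruits means roughly 8% to 23% of those eligible (100/1300 and 300/1300), so these cluster sizes are feasible.

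**Step 3. What these ICCs mean.** The standard deviation of prevalence between practices is √(ICC × p(1−p)). At p = 5% this is 0.7 percentage points for ICC 0.001, 2.2 points for 0.01 and 3.1 points for 0.02. The last row of the table therefore describes large differences between practices. As a further illustration, suppose half the practices had 5% prevalence and half 7.5%. The standard deviation is then 1.25 points and the ICC is 0.0125²/(0.0625 × 0.9375) ≈ 0.0027. With 150 to 300 recruits per practice the design effect is 1.4 to 1.8, and the interval is 18% to 34% wider. The protocol offers 5% to 7.5% as uncertainty about overall prevalence, not as a spread between practices, so this only sets a scale.

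**Step 4. Per pathway, n = 1500.** Under independence the width is 0.0221 at 5% and 0.0267 at 7.5%. Take 20 practices of 150 and ICC 0.01:

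- If each practice fed one pathway (10 practices of 150 per pathway), the design effect is 2.49 and the widths are 0.0348 and 0.0421.
- If each practice split evenly between pathways (20 practices of 75 per pathway), the design effect is 1 + 74 × 0.01 = 1.74 and the widths are 0.0221 × √1.74 = 0.029 and 0.0267 × √1.74 = 0.035.

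The document does not say which applies.

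**The case against.** The strongest reply is that the size of the effect is entirely assumed. Nothing in the document favours one ICC over another, and with 30 practices and ICC 0.001 the width barely moves. Everyone recruited has obesity, type 2 diabetes or hazardous drinking, so differences between practices in how common those risk factors are do not carry straight into prevalence among recruits. In addition, no power calculation or decision threshold depends on the width, and 0.025 at 5% (about ±1.2 points) is still a usable estimate. All of this stands. It limits the size of the point, but does not remove the independence assumption behind the printed figure.

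A second reply is that interval methods belong in a statistical analysis plan that is not shown. That stands for the analysis method, and its absence here is no fault. It does not dispose of the printed planning width, which a later clustered analysis would leave uncorrected.

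A reader might infer that the error bars for each pathway's yield are too narrow, or that the study's intervals will under-cover. The document supports neither. It prints no interval for yield or for a difference between pathways, and it names no interval method. A reader might also infer that whole practices feed one pathway, which would enlarge the effect on a comparison. The article does not say how pathways are allocated. Finally, as printed, the 0.06 is too wide rather than too narrow, so the charge of optimism applies to the 0.019 and to the 0.016 that was probably meant.

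**Conclusion.** The point holds for the planned prevalence width. That width is a simple-random-sample calculation applied to people recruited through practices, and one of its two printed figures does not reproduce. With any positive within-practice correlation the stated precision is too favourable. Across the assumed scenarios the interval is between about 5% wider (√1.10) and 2.6 times as wide (√6.98), with a middle case of about 1.6 times (√2.49). These factors rest on assumed ICCs and equal cluster sizes, and the true value could lie at the negligible end. Nothing here shows that a conclusion of the study would change. The correction is nevertheless worth making, because the protocol relies on the figure to describe the sample as precise.

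**What to change.** 1. Correct the 0.06; if 0.016 was meant, print that.
2. State the expected or actual number of practices, an assumed ICC with a range, and the resulting design effect. Restate the expected width overall and for about 1500 per pathway, saying whether pathways are allocated by practice or within it.
3. Compute the prevalence interval, and any interval reported for pathway yield or uptake, allowing for practice. A random practice intercept or a cluster-robust variance would serve. With perhaps 10 to 30 practices, the robust variance needs a small-cluster correction.

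Practice is not among the items in Table 1, but it should be identifiable, because Data collection and record keeping describes collection in practice electronic records and upload under agreements with individual practices. It is worth confirming that the identifier reaches the analysis dataset.

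The cost is a less favourable stated width, a small amount of analysis work, and no change to recruitment.
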